### Statistical analysis

The research hypothesis is that there is a difference in DPPC (PC32:0) fractional concentration between the conservative and usual oxygen groups. The primary endpoint is percentage DPPC (PC32:0) relative to total PC composition (% of total PC in surfactant) at 48 hours. For the primary analysis, we will use a multiple regression model adjusted for baseline to investigate the difference between the conservative and usual oxygen groups. If data are not normally distributed, we will investigate whether a log transformation improves normality. We will also perform an adjusted analysis to address clinical heterogeneity, using multiple regression, with up to 10 variables including the following baseline variables: age, gender, body mass index, percentage of PC32:0 in relation to total PC composition at admission, clinical conditions (e.g., sepsis, pneumonia) and concentration of inspired oxygen required at admission. We will also perform descriptive subgroup analysis for group differences and present them as box and whisker plots and scatter plots. As samples are collected from time points T=0, T=48 and T=72 hours as a secondary analysis, we will also investigate the use of mixed models to look at the difference between groups over time.

For the secondary outcomes of surfactant index; surfactant PC32:0, PC32:1, PC30:0; surfactant total phosphatidylcholine and PC32:0
*methyl-*D
_9_ choline enrichment; surfactant total lysoPC and lysoPC16:0 concentrations, composition and
*methyl*-D
_9_ choline enrichment and surfactant oxidised PC composition and concentrations (all measured at 48 hours), we will investigate the difference between groups using a two-sample t-test or Wilcoxon- Mann-Whitney test depending on the normality of data. If appropriate, adjusted analyses will also be performed as specified for the primary endpoint. The above will be repeated for the analysis of individual redox/oxidative stress markers listed above.

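### The secondary surfactant and redox outcomes have an unadjusted t-test or rank test, chosen by observed normality, as their main analysis; the primary endpoint's regression on a fixed scale would serve better

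*Protocol article*

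**What the plan says.** All of this is in the Statistical analysis section of the protocol article unless another section is named.

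- **Primary endpoint.** "The primary endpoint is percentage DPPC (PC32:0) relative to total PC composition (% of total PC in surfactant) at 48 hours". For it, "we will use a multiple regression model adjusted for baseline to investigate the difference between the conservative and usual oxygen groups". A further analysis with up to ten baseline variables is planned. On scale: "If data are not normally distributed, we will investigate whether a log transformation improves normality".
- **Secondary outcomes.** The surfactant index, PC species, enrichment, lysoPC and oxidised PC outcomes share the primary endpoint's time point ("all measured at 48 hours"). The plan for comparing the arms on them reads: "we will investigate the difference between groups using a two-sample t-test or Wilcoxon- Mann-Whitney test depending on the normality of data". The same approach is then extended to the individual redox and oxidative stress markers.
- **Adjustment of secondary outcomes.** "If appropriate, adjusted analyses will also be performed as specified for the primary endpoint".
- **The list itself.** It opens "For the secondary outcomes of surfactant index; surfactant PC32:0, PC32:1, PC30:0; surfactant total phosphatidylcholine and PC32:0", where the last item refers to D9-choline enrichment. The first mention of PC32:0 carries no unit.
- **Outcome measures section.** PC32:0 appears as the primary percentage, as one term in the numerator of the surfactant index, and as an enrichment outcome. No other stand-alone secondary outcome for it is defined.

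**The concern.** The protocol uses a baseline-adjusted regression for its primary endpoint and then falls back on a simple two-group test for the mechanistic outcomes, although samples at T=0 and a set of baseline covariates are collected for everyone. Two things are at stake.

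First, the quantity estimated. A t-test compares means, whereas a Wilcoxon-Mann-Whitney test compares ranks. If the observed shape of each marker decides between them, a panel of lipid and redox readouts will mix the two, and no criterion for the choice is stated. Objectives 1 and 2 are to quantify and compare between groups, which calls for effect estimates of a known and consistent kind.

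Second, precision. With about 45 evaluable patients per arm, ignoring a prognostic baseline value or covariate costs power.

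A smaller, separate point is that PC32:0 on the secondary list cannot be matched to a defined outcome.

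**Working it through.** **Inputs.** From Sample size calculation: SD 12.1 or 4.3, difference 8.4 or 3.0 percentage points, N=90 (45 per arm), two-sided alpha 0.05, power 90%, 10% dropout, 100 recruited. The correlation r between baseline and the 48-hour value is not given, so it is assumed over 0 to 0.7.

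**1. The plan's own figure.** The standard error of the difference is SD × √(2/45) = SD × 0.2108.
- SD 12.1: 12.1 × 0.2108 = 2.551; 8.4/2.551 = 3.293; 3.293 − 1.960 = 1.333, so power is 90.9% (90.3% with the noncentral t).
- SD 4.3: 4.3 × 0.2108 = 0.9065; 3.0/0.9065 = 3.309; 3.309 − 1.960 = 1.349, so power is 91.1% (90.5% with the noncentral t).
- 90/(1 − 0.10) = 100.

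The sample size reproduces and is not in question.

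**2. Cost of leaving out a prognostic baseline.** Adjustment multiplies the residual SD by √(1 − r²). An effect that the adjusted model detects with 90% power equals (1.960 + 1.282) adjusted standard errors. The unadjusted test then has power Φ(3.242 × √(1 − r²) − 1.960), whatever the SD.

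| Assumed r | √(1 − r²) | Argument of Φ | Power of unadjusted t-test | Patients needed relative to adjusted, 1/(1 − r²) |
|---|---|---|---|---|
| 0 | 1.000 | 1.282 | 90% | 1.00 |
| 0.3 | 0.954 | 1.132 | 87% | 1.10 |
| 0.5 | 0.866 | 0.847 | 80% | 1.33 |
| 0.7 | 0.714 | 0.355 | 64% | 1.96 |

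This does not carry over to D9-choline enrichment: before the infusion the label should be close to absent (an inference from the tracer design), so the T0 value has little or nothing to explain.

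**3. Type I error of the normality-based choice.** There were 20,000 null simulations with 45 per arm. The assumed rule was a Shapiro-Wilk test at 0.05 in either arm, leading to the Wilcoxon test if it rejects.
- Fixed rule followed: 5.0% for normal data and 5.0% for lognormal data.
- Smaller of the two p-values reported: 5.8% and 6.9%.

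A fixed rule does no harm to type I error. The harm lies in the changing quantity and in the room left for selection when no rule is stated.

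**4. The PC32:0 entry.** The entry reads "For the secondary outcomes of surfactant index; surfactant PC32:0, PC32:1, PC30:0". The three species named after the index are exactly those in the index numerator in Outcome measures. They may be a loose listing of its components, or separate outcomes as percentages or as concentrations. The text does not settle which.

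**The case against.** The strongest reply is that adjustment is already provided for, that much of the rest is detail for a statistical analysis plan, and that the practical harm is small. Part of this stands. Adjusted analyses are foreseen, but as an addition, under a condition that is not spelled out, so the unadjusted test remains the main one. Particular interval methods and model terms can be left to the analysis plan. The choice of test and the rule for choosing it are stated in the article, however, so they are not missing detail. A Wilcoxon test can also be accompanied by a Hodges-Lehmann shift with an interval, so a rank test need not mean a bare p-value.

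A second reply concerns the remedy, and it stands. The Interventions section aims for the first samples within 24 hours after randomisation, so T0 may already reflect the allocated oxygen. Adjusting for it could remove part of the effect. This limits the use of T0, but not of covariates recorded before randomisation.

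Three stronger readings are tempting and are not supported:

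- **That the primary endpoint is tested twice, with competing results.** A reader might infer this from the PC32:0 entry. If it meant the percentage, and either the adjusted or the unadjusted test could support a claim, simulated type I error would be 6.4%, 6.9% and 8.2% at r = 0.3, 0.5 and 0.7. But the entry has no unit, it matches the index numerator, and the section already designates the baseline-adjusted regression as the primary analysis. Precedence is therefore fixed.
- **That the log provision will shift the primary off its percentage-point scale.** The provision asks only whether logging improves normality. On the plan's ARDS figures (mean 35.6, SD 12.1) a normal variable has skewness near 0 raw and roughly −1.5 after logging (about −1.1 to −1.8, depending on how near-zero values are handled). Logging would rarely pass that test.
- **That every mechanistic outcome loses precision.** This fails for enrichment, and for any outcome whose baseline correlation is near zero.

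**Conclusion.** The point holds in limited form. The main analysis of the secondary surfactant and redox outcomes is unadjusted, and its type is chosen from the data without a stated criterion, so the quantity compared can vary between markers. The loss of power, from 90% to about 87%, 80% or 64%, rests on assumed correlations of 0.3, 0.5 and 0.7 and on 45 evaluable patients per arm. It is nil at a correlation of 0. To the extent that T0 proves unsuitable for adjustment, the gain must come from pre-randomisation covariates, whose explanatory strength the article does not give. Type I error is not the issue under a fixed rule. The PC32:0 entry is an ambiguity between two sections, not a demonstrated second test of the primary endpoint. The sample size and the primary analysis are unaffected. The change is worth making because it uses data already collected and costs almost nothing.

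**What to change.** 1. Make the regression model the main analysis of each secondary surfactant and redox outcome, adjusted for covariates fixed before randomisation.
2. Include the T0 value only as it is handled in the primary model, after deciding whether a sample taken up to 24 hours after randomisation can serve as a baseline. Omit it for D9-choline enrichment.
3. Set the scale of each outcome in advance: raw percentage points for composition, log for ratios (including the surfactant index) and concentrations.
4. Report estimates with confidence intervals, and delete the choice of test by normality.
5. Define PC32:0 on the secondary list, for example as an index component or a concentration, or remove it if it means the primary percentage. Bring Statistical analysis and Outcome measures into line.

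The cost is a change of wording and a little more programming, with no new samples or patients. The downside is that log-scale results are reported as ratios. Recruitment has begun, so the change should be made before outcome data are examined by group.

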### Data management

The clinical data collection will be enhanced within the ICNARC CMP research platform. Additional data collection will be obtained beyond the standard data collection by the UK-ROX clinical trial. The additional data will include baseline demographic variables, ventilation, and oxygenation parameters. The principal investigator will oversee and be responsible for data collection, quality, and recording. The nested CMP research platform enables data collection to be incorporated within the ICNARC routine CMP data collection process, streamlining data linkage. Study data will be made available online at the time study results dissemination.

### Ethics approval and study management

The study is sponsored by the University Hospital Southampton NHS Foundation Trust. The study is approved by HRA and the London Bromley Research Ethics Committee, REC: 22/LO/0877 and IRAS: 320671. The study is registered on ISRCTN registry, ISRCTN61929838 (
https://doi.org/10.1186/ISRCTN61929838). The MecROX study is managed by the Southampton Clinical Trials Unit (CTU) and Sponsored by the University Hospital Southampton. Chief Investigator will ensure all study personnel are appropriately orientated and trained, oversee recruitment and report to the trial safety monitoring committee.

### Study dissemination

The findings of this study will be presented locally, nationally, and internationally in intensive care and respiratory conference and society meetings and published through peer review journals.

### Study status

As of 19
^th^ of February 2024, both sites are open for recruitment and recruited 25 participants so far.

### Strengths of the study

This is the first study to investigate the lung surfactant metabolism and systemic redox markers from mechanically ventilated patients with different oxygen targets providing a mechanistic in-vivo evaluation of oxidative stress and redox biology in critical illness. Results will inform underlying mechanisms of hyperoxia and hyperoxemia.

## Discussion

MecROX is a mechanistic study that aims to determine the mechanisms underlying hyperoxia and hyperoxemia induced lung surfactant and whole-body redox changes in-vivo. While oxygen therapy is essential for critically ill mechanically ventilated patients, there are potentially many harmful effects from hyperoxia, as demonstrated by several studies of hospitalised patients with acute conditions. Oxygen toxicity due to hyperoxia/hyperoxaemia is a well-recognised phenomenon in animal studies. Hyperoxaemia may exacerbate whole-body oxidative stress leading to cell death, autophagy, mitochondrial dysfunction, biogenetic failure with eventual multi-organ failure resulting in poor clinical outcomes. However, in-vivo human models evaluating hyperoxia-induced organ damage in mechanically ventilated patients are lacking. Decreased surfactant synthesis due to cellular apoptosis and increased surfactant breakdown by oxidation/hydrolysis can result in surfactant deficiency during states of increased oxidative stress. However, the influence of hyperoxia on direct surfactant damage and whole-body redox status has never been evaluated before in relation to various oxygen targets. It is critical to assess the alveolar environment to quantify the oxidative stress and redox imbalance to minimise surfactant breakdown to prevent worsening lung atelectasis and hypoxaemia.

This proposed study will mechanistically evaluate the in-vivo surfactant metabolism using a novel stable isotope technique and various platforms of mass spectrometry analytical methods. Surfactant phospholipid breakdown through hydrolysis (lysophospholipids) and oxidation (oxidised phospholipids) and redox disequilibrium (‘reactive species interactome’) will be quantified from sequential plasma and bronchial samples using an array of analytical platforms. These assessments will help characterise the alveolar and systemic redox status during different oxygen targets to stratify patients according to evidence of oxidative surfactant damage that may be responsive to targeted administration of therapies to minimise oxidative stress in the future.

## Conclusions

This observational study aims to characterise in-depth the molecular mechanisms relating to oxygen therapy in mechanically ventilated patients enrolled in the UK-ROX clinical trial receiving oxygen therapy to two different target targets. The study will collect serial biological samples to evaluate dynamic surfactant phospholipid concentrations, composition, synthesis, catabolism, and global assessment of whole-body oxidative stress and redox status (markers of the “reactive species interactome”). By doing so, the study aims to provide a mechanistic link between pathophysiology and clinical outcomes in critically ill intensive care patients receiving oxygen therapy.

## Data Availability

No data are associated with this article. Once the study analysis is complete and the results of the study are published, the anonymised data will be made available via an online repository according to the NIHR data sharing policy. The full detailed protocol is available upon request to the corresponding author.
